### Data collection, management, and analysis

#### Data collection and management

The Independent Tape Rater Scale (ITRS) was used to assess proficiency in motivational interviewing and implementation effectiveness. The ITRS is a well-validated tool for assessing two key factors: adherence and competence [26]. Confirmatory factor analysis has supported the two-factor structure of the ITRS [26], and excellent levels of inter-rater reliability have been found for both motivational interviewing adherence (mean ICC .89; range .66–.99) and competence (mean ICC .85; range .69–.97) [26].

The lead developer of the MIBI protocol (co-author SM) oversaw the selection, training, calibration, and supervision of the project’s 15 MIBI raters, who were blinded to study condition. Booster trainings and recalibration of the raters were conducted in between cohorts. Consistent with the established guidelines promoted in the motivational interviewing assessment: Supervisory Tools for Enhancing Proficiency [93], BI staff were considered to have demonstrated proficiency when at least half of the 10 motivational interviewing consistent items were rated 4 or greater on a 7-point scale for both adherence and competence. Submissions of MIBI sessions from BI staff and ratings from MIBI raters were enabled via a secure, Web-based implementation tracking system adapted from one used in our prior implementation research [94]. In addition to enabling MIBI raters to stream the audio files rather than download, an important security feature, the Web-based system allowed MIBI raters to enter adherence and competence ratings directly into the secure and backed-up database located on RTI’s servers.

As shown in Table 7, ASO staff participating in the ISF Experiment were invited to complete staff surveys at three time points: the exploration phase assessment at month zero, the implementation phase assessment at month 13, and the sustainment phase assessment at month 19. In addition to collecting background information for each participant (e.g., age, race, ethnicity, gender, educational level, tenure in profession, tenure with organization, salary, substance use recovery status), staff surveys assessed several domains theorized to be of importance—namely innovation values-fit, tension for change, implementation climate, implementation readiness, and leadership engagement—and assessed both the number of clients screened for substance use and the number clients to whom a brief intervention for substance use was delivered.

Given the professional level of ASO staff, surveys were self-administered. However, as a means of ensuring the highest quality data possible, surveys were Excel-based to help prevent common data quality issues like out-of-range responses. In addition to these real-time quality assurance measures, all staff surveys received quality assurance reviews from a project coordinator. When issues were identified, the project coordinator contacted the participant via email and/or phone to resolve the issue. Once the staff survey was complete, it was exported into a master database on one of RTI’s secure access-controlled servers that are backed up nightly. Each survey required about 30–45 min to complete, and participants received a $25 e-gift card as compensation for their time.

### Statistical methods

Statistical analyses will be conducted using an intention-to-treat analysis approach, which will analyze all ASOs as randomized. Hot-deck imputation [95, 96] will be used to address missing data issues, which are anticipated to be minimal (i.e., less than 5%). Analyses will be conducted using HLM software [97], which is well-suited for handling clustered data (i.e., time nested within staff, nested within organization). Analyses will be conducted in the order outlined in Table 1. In addition to reporting the coefficient, standard error, 95% confidence interval, and *p* value, results will also include effect size indicators.

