### Outcomes

Table 7 describes the three staff-level outcome measures (i.e., time-to-proficiency, implementation effectiveness, and level of sustainment) used to examine the extent to which the ISF strategy serves as an effective adjunct to the ATTC strategy. Additionally, Table 7 describes the two staff-level measures (i.e., personal recovery status and motivational interviewing experience) and four organizational-level measures (i.e., readiness for implementing change, implementation climate, leadership engagement, and tension for change) that have been hypothesized as moderators of the relationship between organizational condition assignment (ATTC vs. ATTC + ISF) and each respective primary outcome measure.

**Table 7 Tab7:** Instruments, instrument-related procedures, and measures

Measurement instrument	Measurement instrument time points and procedures					
	Staff survey #1 (t = month 0)	Preparation phase assessment (t = months 1–6)	Implementation phase assessment (t = months 7–12)	Staff survey #2 (t = month 13)	Staff survey #3 (t = month 19)	Measure name (purpose) Description
Independent Tape Rater Scale [26]		X^a^				Time to proficiency (preparation outcome) A continuous staff measure representing the number of days between completion of the workshop training by BI staff and their demonstration of proficiency [26, 30] in the motivational interviewing-based brief intervention (MIBI)
Independent Tape Rater Scale [26]			X^b^			Implementation effectiveness [31] (implementation outcome) A continuous staff measure representing the sum of the standardized cumulative number of MIBIs delivered by BI staff (i.e., consistency) and the cumulative integrity score of their delivery of the MIBI (i.e., quality)
Staff survey	X^c^			X^c^	X^c^	Level of sustainment (sustainment outcome) A continuous staff measure (no specified range) that represents the number of MIBIs a BI staff self-reports having delivered during the past 6 months
Staff survey	X^c^			X^c^	X^c^	Motivational Interviewing Experience (moderator variable) A staff measure indicating a BI staff’s perception of their motivational interviewing experience (0 = none, 1 = beginner, 2 = intermediate, 3 = advanced, 4 = expert)

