#### Sample size

Sample size for the ISF Experiment was determined via power analyses with Optimal Design Software [88]. We assumed an equal number of BI staff (2 per ASO) and an intraclass correlation coefficient of .05. With 78 BI staff nested within 39 ASOs, there is 80% power to detect statistically significant (p < .05) differences when the effect size is .67 or greater.

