### Key Limitations and Strengths of the ISF Experiment

The SAT2HIV Project’s ISF Experiment has limitations and strengths that are important to acknowledge. Key limitations include (1) the sustainment phase observation period being limited to 6 months, (2) the level of sustainment being limited to self-reports, and (3) cost-effectiveness not being examined. These limitations, however, are outweighed by the project’s many strengths.

Key strengths include the ISF Experiment’s (1) highly rigorous design as a randomized, hypothesis-driven experiment using psychometrically sound measures, (2) focus on the high-need setting of ASOs, (3) large sample size of 39 ASOs with 4-6 staff per ASO, (4) large geographic representation (23 states and the District of Columbia), and (5) examination of multiple phases of the EPIS continuum (preparation phase, implementation phase, and sustainment phase).

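### Hot-deck imputation is the only missing-data method, with no stated allowance for imputation uncertainty and no rule for BI staff who leave before the month-19 sustainment report

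*Protocol article*

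**What the plan says.** The Statistical methods section deals with missing data in one sentence: "Hot-deck imputation [95, 96] will be used to address missing data issues, which are anticipated to be minimal (i.e., less than 5" per cent. The sentence makes no exception for outcomes and names no other method. The same section sets the analysis set, "Statistical analyses will be conducted using an intention-to-treat analysis approach, which will analyze all ASOs as randomized", and the reporting standard: "In addition to reporting the coefficient, standard error, 95% confidence interval, and" the p value, with effect size indicators added. The software is a multilevel modelling package.

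Level of sustainment, one of the three staff-level outcomes, is defined in Table 7 as a measure that "represents the number of MIBIs a BI staff self-reports having delivered during the past 6 months". The value for the sustainment phase comes from the last survey, "the sustainment phase assessment at month 19". The authors list among the limitations "the level of sustainment being limited to self-reports".

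Under Sample size, the clustering assumptions are given as "We assumed an equal number of BI staff (2 per ASO) and an intraclass correlation coefficient of .05". The power statement, whose threshold is a standardized difference of .67, reads "With 78 BI staff nested within 39 ASOs, there is 80% power to detect statistically significant (p < .05) differences when the effect size is". That paragraph makes no allowance for missing outcomes. The article does not mention staff turnover or replacement of BI staff.

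**The concern.** There are two separate issues.

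**Precision.** A hot deck copies a respondent's value into each gap. If the completed file is analysed as though every value had been observed, the model sees 78 independent pieces of information where there are fewer. Standard errors come out too small, intervals too narrow and p values too low. If donors are drawn from both arms together, the filled values pull the arms towards each other and the estimate shrinks.

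**Meaning of the sustainment outcome.** The rationale for the primary outcomes describes sustainment as MIBIs delivered during the sustainment phase. A BI staff member who has left the ASO delivers none there afterwards. If that person does not answer the month-19 survey, the value is missing, and a hot-deck donor is by definition someone who did answer. ISF works on the organization, so an effect on staff retention is conceivable. Filling leavers from respondents would remove that part of its effect. With two BI staff per ASO, one leaver is half of a cluster's outcome data.

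**Working it through.** **1. The plan's own figure.** Inputs from Sample size: J = 39 ASOs, n = 2 staff, ICC ρ = .05, α = .05 (taken as two-sided). The noncentrality is λ = J·d² / {4[ρ + (1 − ρ)/n]} = 39·d² / (4 × 0.525) = 39·d²/2.1. At d = .67, λ = 39 × 0.4489/2.1 = 8.34. On 1 and 37 df this gives 80.3% power, and the smallest detectable effect at 80% is 0.668. The stated .67 reproduces, for complete data.

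**2. What the ceiling means.** 0.05 × 78 = 3.9, so under 5% allows at most 3 BI staff.

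**3. Within-arm donors, one draw, analysed as observed (assumed reading).** With a fraction m missing at random, and ignoring the small clustering, the true variance of an arm mean is approximately (σ²/N)·[1/(1 − m) + m], while the analysis reports about σ²/N. The ratio of reported to true SE is therefore 1/√[1/(1 − m) + m]. At m = .05 this is 1/√(1.0526 + 0.05) = 0.952. The actual type I error is then P(|t₃₇| > 2.026 × ratio). The simulation used 19 against 20 ASOs (assumed split) with 2 staff each, ICC .05, no true effect, a t-test on cluster means and 20,000 trials per rate.

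| Missing | SE ratio, formula | Type I, formula | SE ratio, simulated | Type I, simulated |
|---|---|---|---|---|
| 0% | 1.000 | 5.0% | 1.000 | 4.8% |
| 2% | 0.980 | 5.4% | 0.972 | 5.3% |
| 5% | 0.952 | 6.1% | 0.945 | 6.3% |
| 10% | 0.909 | 7.4% | 0.901 | 7.3% |
| 20% | 0.830 | 10.1% | 0.823 | 10.3% |
| 30% | 0.761 | 13.2% | 0.749 | 13.6% |

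A further simulation with exactly 3 of 78 missing gave 5.7% (negative binomial counts, mean 8, k = 1) to 5.9% (normal). The rows above 5% are assumed rates; the article does not predict them.

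**4. Pooled donors.** A fraction m of each arm takes the pooled mean on average, so a true difference Δ becomes about Δ(1 − m). For an assumed Δ of 8.0 MIBIs this is 8.0 × (1 − 3/78) = 7.7 at the ceiling and 8.0 × 0.8 = 6.4 at 20% missing. Type I error with pooled donors and 3 missing was 4.9%.

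**5. Leavers and sustainment (all counts assumed).** Suppose staff who stay deliver μ in both arms, leavers deliver 0, and no leaver responds. With leaving proportions q₀ (ATTC) and q₁ (ATTC + ISF), the difference counting leavers as 0 is μ(q₀ − q₁). Filling leavers from respondents who stayed gives 0.

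- μ = 10, q₀ = .30, q₁ = .15: 1.5 MIBIs against 0. Reversing the two rates gives −1.5 against 0.
- μ = 8, q₀ = .30, q₁ = .10: 1.6 against 0.
- Equal 5% loss, stayers' means 10 and 13: 0.95 × 3 = 2.85 against 3.0.
- At the ceiling, all 3 leavers in an arm of 38 staff, μ = 8: 8 × 3/38 = 0.63 MIBIs. With k = 1 the SD is √(8 + 8²) = 8.5, so this is about 0.07 SD, against a detectable effect of .67.

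**The case against.** The strongest reply is that the article does not describe a single imputation. It names a family of methods and cites two sources. The number of draws, the donor classes and the variance method are not given, a hot deck can be run with multiple draws, and a condensed article may leave such detail to a fuller plan. That stands. A reader might infer that the plan uses one draw and that its error bars are therefore wrong, but the text does not support that as a fact. What can be judged is what is fixed here: one method for all missing data, with no word on how its uncertainty reaches the promised intervals.

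The reply also notes that the effect on precision is small at the protocol's own rate. That stands too. The figures of 10% and above need missingness that the article does not anticipate.

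Finally, no section mentions departures, and nothing limits the month-19 survey to current employees. It is electronic, self-administered and compensated, so a leaver may answer and report a true count. The other two outcomes rest on rated sessions, not on this survey. So a reader might infer that departed staff will be filled from active staff and that sustainment will be overstated in both arms, but this needs leavers in both arms, non-response by them, and donors who are still delivering. None of these is documented. Counting leavers as 0 is also partly a choice of estimand, since Table 7 defines the outcome by what the staff member reports.

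What remains is that a leaver who does not answer has no value, that the only named remedy supplies a respondent's count, and that multiple draws from respondents would not change this.

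**Conclusion.** The point holds in a limited form. The protocol relies on hot-deck imputation alone, on an expectation of under 5% missing for which it gives no basis. Table 8 shows that the first cohort had finished its sustainment phase in June 2016, before the article appeared in November 2017, yet only an anticipation is offered.

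If the method is one within-arm draw analysed as observed, type I error is about 6% instead of 5% at the ceiling, with standard errors about 5% too small. It becomes serious only if missingness runs well past the ceiling: about 10% at 20% missing and 13% at 30%. These results assume data missing at random and a cluster-mean analysis. Pooled donors would cost a few per cent of the effect at the ceiling.

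For level of sustainment, an effect of ISF on retention could be masked. The direction depends on which arm loses more staff. The size is small if no more than 3 staff are missing, and could reach 1.5 MIBIs or so per staff member under the assumed differential turnover.

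**What to change.** - For outcomes, replace the hot deck with multiple imputation within arm, using baseline and phase data. Alternatives are multiple hot-deck draws combined by Rubin's rules, or maximum likelihood on the observed outcomes in the multilevel model already planned.
- State how imputation uncertainty enters the SE, the 95% CI and the p value.
- Report missingness and BI staff turnover by arm.
- Add a sensitivity analysis of level of sustainment that counts MIBIs after departure as 0. This needs departure dates, which the article does not say are collected.

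The cost is a change of wording, a little more programming and slightly wider intervals. As a guide, analysing observed outcomes only at 5% missing (average cluster size 1.9) widens the SE by √[(0.05 + 0.95/1.9)/(0.05 + 0.95/2)] = √(0.55/0.525) = 1.024, about 2%. The detectable effect moves from 0.67 to about 0.68. At 20% and 30% missing the same approximation gives 0.74 and 0.79, a loss of information that a single draw would conceal.

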### Monitoring

#### Data monitoring

The ISF Experiment was conducted under the auspices of RTI International’s IRB. The Principal Investigator of the ISF Experiment, however, assumes ultimate responsibility for the project’s data and safety monitoring.

#### Harms

Minimal risks are associated with the study and are limited to the potential breach of confidentiality. All adverse events are reported to the Principal Investigator within 24 h. Adverse events are reported to the IRB within 2 weeks of the Principal Investigator’s awareness of the event, with serious adverse events reported within 1 week.

#### Auditing

RTI International’s IRB conducts annual and random audits to assess adherence to federal human subjects protection regulations and to ensure that the rights and welfare of human subjects are protected.

### Ethics and dissemination

#### Research ethics approval

The ISF Experiment was reviewed and approved by RTI International’s IRB, under Federalwide Assurance No. 3331 from the Department of Health and Human Services’ Office for Human Research Protections.

#### Protocol amendments

Any protocol modification that may affect the conduct of the study, potential benefit to the participants, or participant safety requires a protocol amendment. All amendments were submitted to RTI International’s IRB for approval, with no protocol modification implemented until after notification of IRB approval.

#### Consent

In addition to having ASOs complete a project participation agreement, written consent was obtained from both leadership staff and BI staff. The project’s IRB-approved informed consent form was emailed to potential participants along with a password-protected assurance of consent form, the password for which was sent in a separate email. Individuals could not participate in the project without first completing the form.

#### Confidentiality

Information provided as part of the study is confidential and not shared with anyone outside the study. The exception, however, is if the participant has a plan to harm himself or herself or another specific person. Efforts to protect participant confidentiality include the following: (1) use of a unique participant ID number only accessible to the ASO study staff and a limited number of RTI study staff, (2) any study document (paper or electronic) that contains both the participant name and ID number is securely stored (e.g., locked file cabinet in a secure building, folder located on a password-protected server in a secure building), and (3) when study results are presented at meetings or published in journals, no identifying participant information will be included. Except for the assurance of consent form, which is required to be stored for at least 3 years after study completion, documents with identifying information will be destroyed within 90 days of study completion.

#### Access to data

Access to data is restricted during the active data collection period and is limited to the Principal Investigator, data coordinators, statistician, and statistical programmer. Following the completion of the study, a public access dataset will be created and made available upon request to the Principal Investigator.

#### Ancillary and post-trial care

No ancillary or post-trial care is planned.

#### Dissemination policy

Irrespective of the magnitude or direction of effect, study findings will be disseminated. Dissemination efforts will include presentations at professional scientific conferences and publication in peer-reviewed journals. To the extent possible, we will seek to ensure study publications are open access (i.e., available online to readers without financial, legal, or technical barriers beyond those inseparable from gaining access to the internet).

## Discussion

In this paper, the study protocol for the SAT2HIV Project’s ISF Experiment, a cluster-randomized trial on the effectiveness of the ISF strategy as an adjunct to the ATTC strategy (Aim 2 of the parent SAT2HIV Project), has been described in accordance with the SPIRIT guidelines [21, 22]. In the sections below, we highlight and discuss: (1) key trial-relevant events (anticipated and unanticipated) that have occurred to date, (2) key limitations and strengths of the ISF Experiment, and (3) key anticipated impacts of the ISF Experiment.

### Trial-relevant events that have occurred to date

Table 8 summarizes key anticipated and unanticipated trial-relevant events that have occurred and that help illustrate the ISF Experiment’s progression and changing outer context.

**Table 8 Tab8:** Key trial-relevant events to date

Calendar year	Calendar month	Project year	Project month	Key project-relevant events
2014	July	Year 1	Month 1	The grant received a $565,695 (16%) reduction in its total budget, which resulted in reducing the targeted number of participating organizations and dropping a specific aim on the cost-effectiveness of the ISF intervention
	August		Month 2	
	September		Month 3	
	October		Month 4	
	November		Month 5	The Principal Investigator ([name]) moved from Chestnut Health Systems to RTI International The grant was relinquished to the National Institute on Drug Abuse (NIDA)
	December		Month 6	
2015	January		Month 7	Cohort 1: Preparation phase initiated
	February		Month 8	The grant, minus the costs incurred during the first 5 months of the grant, was awarded to RTI International with [name] as the Principal Investigator
	March		Month 9	
	April		Month 10	
	May		Month 11	
	June		Month 12	Cohort 1: Preparation phase completed
	July	Year 2	Month 13	Cohort 1: Implementation phase initiated The updated United States National HIV/AIDS Strategy was released
	August		Month 14	
	September		Month 15	
	October		Month 16	
	November		Month 17	
	December		Month 18	Cohort 1: Implementation phase completed
2016	January		Month 19	Cohort 1: Sustainment phase initiated Cohort 2: Preparation phase initiated
	February		Month 20	
	March		Month 21	
	April		Month 22	
	May		Month 23	
	June		Month 24	Cohort 1: Sustainment phase completed Cohort 2: Preparation phase completed
	July	Year 3	Month 25	Cohort 2: Implementation phase initiated
	August		Month 26	
	September		Month 27	
	October		Month 28	
	November		Month 29	
	December		Month 30	Cohort 2: Implementation phase completed

*ISF* implementation and sustainment facilitation

### Key Limitations and Strengths of the ISF Experiment

The SAT2HIV Project’s ISF Experiment has limitations and strengths that are important to acknowledge. Key limitations include (1) the sustainment phase observation period being limited to 6 months, (2) the level of sustainment being limited to self-reports, and (3) cost-effectiveness not being examined. These limitations, however, are outweighed by the project’s many strengths.

Key strengths include the ISF Experiment’s (1) highly rigorous design as a randomized, hypothesis-driven experiment using psychometrically sound measures, (2) focus on the high-need setting of ASOs, (3) large sample size of 39 ASOs with 4-6 staff per ASO, (4) large geographic representation (23 states and the District of Columbia), and (5) examination of multiple phases of the EPIS continuum (preparation phase, implementation phase, and sustainment phase).

